## Abstract

**Introduction:** Tuberculosis (TB) is a major infectious disease that seriously endangers human health and female reproduction. In our previous study, 10.4% of infertile patients preparing for *In vitro* fertilization and embryo transfer (IVF-ET) had prior pulmonary TB (PTB) as detected on chest X-ray (CXR) screening. Among them, 81.8% did not receive anti-TB treatment. It remains unclear whether infertile women with untreated prior PTB have latent TB infection (LTBI) and whether LTBI affects IVF-ET outcomes. In this study, we aim to analyze the relationship between LTBI and pregnancy outcomes following IVF-ET in patients with untreated prior PTB.

**Methods and Analysis:** We designed a prospective cohort study of 1,200 infertile women with CXR findings suggestive of old-healed untreated TB, who are preparing for IVF-ET. Patients with a history of active TB and anti-TB treatment will be excluded. Interferon-gamma release assay (IGRA) will be used in patients with CXR findings suggestive of old-healed untreated TB to construct a cohort of IGRA-positive and IGRA-negative patients. Participants will undergo IVF-ET. General information, including age, body mass index, infertility causes, and controlled ovarian hyperstimulation protocol, will be recorded. Participants will be followed up during pregnancy. The primary outcome is live birth. Secondary outcomes include the numbers of retrieved oocytes, high-quality embryo rate, clinical pregnancy, number of active TB cases during pregnancy, and miscarriage.

**Ethics and Dissemination:** The study was approved by the Ethics Committee of Peking University Third Hospital [approval number (2020)218-01; approval date: June 19, 2020]. The research results will be disseminated through scientific/medical conferences and published in academic journals.

**Trial Registration:**
ClinicalTrials.gov; identifier: NCT04443283.

## Introduction

Tuberculosis (TB), an infectious disease caused by *Mycobacterium tuberculosis*, seriously affects human health (1, 2). According to a report by the World Health Organization (WHO) in 2020, the global TB incidence rate is ~130 per 100,000 (1). TB may affect the reproductive ability of women and is a common cause of infertility due to blockage of the fallopian tubes or through the involvement of endometrium or ovarian functions (3, 4). Early identification of active TB cases and active anti-TB treatment are essential. However, the onset of TB is insidious, even without symptoms, and some patients may present with “infertility.” *In vitro* fertilization and embryo transfer (IVF-ET) remains the most effective method of treating associated infertility (5).

Although IVF-ET is an effective method, it is necessary to be aware of the harmful effects of TB during pregnancy. Chest X-ray (CXR) is an essential examination before IVF-ET, and active TB should be identified and treated accordingly. Seven cases of miliary TB during pregnancy after IVF-ET have been reported in our previous article (6). Active TB during pregnancy can lead to abortion and increase maternal and neonatal mortality (7–10). Therefore, patients with active TB are not allowed to undergo IVF-ET before receiving a full course of anti-TB treatment. However, during the routine screening before IVF-ET, CXR often reveals signs of prior pulmonary TB (PTB) (6), including fibrous scars, induration, and calcification, due to host interaction during *M. tuberculosis* infection (11, 12). Moreover, this is particularly common in developing countries. Whether anti-TB treatment is needed for so-called “prior pulmonary TB” becomes a clinical dilemma. Moreover, the possible side effects of anti-TB therapy, as well as the delay in pregnancy planning, are also concerns faced by doctors. Recently, we retrospectively analyzed 14,254 infertile patients who had undergone IVF at Peking University Third Hospital in 2017, and 1,487 (10.4%) patients were revealed to have PTB on CXR; among them, 1,239 (81.8%) did not receive anti-TB treatment and were followed to determine pregnancy outcomes (13). The results showed that the untreated prior PTB group had significantly lower clinical pregnancy and live birth rates than the non-PTB group. Moreover, during the follow-up, one patient with CXR findings suggestive of old-healed untreated TB developed miliary TB during pregnancy, which eventually led to abortion (13). We speculate that anti-TB therapy for high-risk patients may contribute to improving pregnancy outcomes. However, further prospective studies are needed to explore the risk factors that may affect pregnancy outcomes in this specific patient population.

Latent TB infection (LTBI) is defined by a positive test for infection and no active TB (14, 15). For high-risk TB patients, timely recognition of LTBI and preventive anti-TB treatment are also important measures for TB prevention and control. The tuberculin skin test (TST) or interferon-gamma release assay (IGRA) is a valuable tool for diagnosing LTBI and identifying people most likely to benefit from treatment (i.e., screening before the start of anti-tumor necrosis factor-α treatment, pre-transplant, and so on). TST has traditionally been used to detect LTBI, but it is known to have limitations. Most notably, its specificity is affected by the Bacillus Calmette–Guérin (BCG) vaccine or non-tuberculous Mycobacterium infection. IGRA (the QuantiFERON-TB [QFT] Gold In-Tube assay and the T-SPOT.TB assay), which measures cellular immune responses to the TB-specific proteins early secreted antigenic target of 6 and 10-kDa culture filtrate protein, has been demonstrated to be as sensitive as or better than TST for diagnosing LTBI, with much higher specificity, and no cross-reaction with the BCG vaccine (16).

Current guidelines recommend screening for LTBI with a TST, IGRA, or both; many also recommend chest radiography. Uzorka et al. reviewed 25 different studies on LTBI and CXR and reported that ~15% of individuals with LTBI had specific lesions on CXR that possibly reflect prior PTB (17). In contrast, ~77.7% of patients with prior PTB based on CXR findings were LTBI-positive. Persons with inactive TB lesions on chest radiographs have a risk of developing progression to active TB, with an incidence of 2.0–13.6 per 1,000 person-years (18). Our previous study showed that the IGRA positivity rate was 75.5% in infertile women with untreated PTB on CXR (unpublished data), which was significantly higher than the average rate of 13–20% previously reported by a study conducted in rural China (19). It remains unclear whether infertile women with untreated prior PTB have LTBI and whether there is a difference in the pregnancy outcomes between those with or without LTBI, and whether prophylactic anti-TB treatment is necessary for LTBI detected prior to IVF-ET in infertile patients.

Here, we hypothesized that adverse IVF-ET pregnancy outcomes in infertile patients might be related to untreated IGRA-positive prior PTB. If confirmed, further scientific evidence is essential to help understand the effect of LTBI on IVF-ET outcomes to optimize the management of LTBI in infertile patients with untreated PTB and update the guidelines.

We designed a prospective cohort study of infertile women who will undergo IVF-ET. IGRA will be performed in patients with CXR findings suggestive of old-healed untreated TB. A cohort of IGRA-positive and IGRA-negative patients will be constructed. Pregnancy outcomes will be followed prospectively, and the relationship between LTBI and pregnancy outcomes will be analyzed.

## Methods and Analyses

### Study Design

This is a prospective cohort study of infertile patients who will undergo IVF-ET from January 1, 2022, to December 30, 2024, at Peking University Third Hospital. According to the sample size calculation, ~1,200 participants will be enrolled. The inclusion criterion is untreated PTB on CXR. The exclusion criteria are (1) active TB, (2) a previous diagnosis of TB, (3) TB other than PTB (e.g., reproductive system TB, renal TB, lymphatic TB), (4) the presence of central nervous system diseases, cancer, or AIDS, (5) long-term oral corticosteroids, immunosuppressants, and inhaled corticosteroid therapy, which may increase the risk of TB, and (6) patients who lack decisional capacity or who cannot guarantee their participation until the end of the study (Table 1). Participants will be divided into IGRA-positive and -negative groups, and the pregnancy outcomes will be followed during pregnancy. We will investigate whether LTBI (positive IGRA) in patients with untreated prior PTB affects the pregnancy outcomes (Figure 1).

**Table 1 T1:** The inclusion and exclusion criteria for selecting the study participants.

**Primary inclusion criteria**	**Primary exclusion criteria**
• Age 18–45 years • Untreated prior PTB based on chest X-ray imaging findings	• Active TB•History of treated previous • TB other than PTB (e.g., reproductive system TB, renal TB, and lymphatic TB) • The presence of central nervous system diseases, cancer, or AIDS • Long-term oral corticosteroids, immunosuppressants, and inhaled corticosteroid therapy • Patients who lack decisional capacity or who cannot guarantee their participation until the end of the study

*AIDS, acquired immunodeficiency syndrome; PTB, pulmonary tuberculosis*.

**Figure 1 F1:**
[figure not shown]
Flow chart of the study design. PTB, pulmonary tuberculosis; CXR, chest X-ray; IVF-ET, *In vitro* fertilization and embryo transfer; IGRA, interferon-gamma release assay.

### Procedures

Infertile patients who will undergo IVF-ET at the Center for Reproductive Medicine of Peking University Third Hospital will be screened. According to the Code of Practice for Assisted Reproductive Technology developed by the Ministry of Health of the People's Republic of China, all patients will undergo routine CXR examination before IVF-ET (20). Patients with abnormal chest images will be referred to the respiratory clinic for consultation, and those with chest imaging abnormalities consistent with prior PTB will be enrolled. Active TB cases will be excluded based on the clinical assessment (contact history, respiratory symptoms related to TB, physical examination), CXR, microbiological studies of sputum/respiratory samples, and endometrial biopsy findings. Moreover, among those with prior PTB based on CXR findings, patients will be excluded if they have a past history of treatment for active TB, and only those with untreated prior PTB will be enrolled. A total of 1,200 infertile patients with untreated prior PTB on CXR will be enrolled.

Participants' baseline characteristics (demographics, clinical characteristics, IVF-ET treatment) will be obtained from the case registration research database, including age, body mass index (BMI), infertility years, causes of infertility, and the controlled ovarian hyperstimulation (COH) protocol. Baseline levels of hormones will also be recorded, including follicle-stimulating hormone (FSH), luteinizing hormone (LH), estradiol (E2), progesterone (P), prolactin, testosterone (T), androstenedione (A), and anti-Müllerian hormone (AMH), and antral follicle count. Follicles after oocyte promotion, hormone levels (FSH, LH, E2, and P) on human chorionic gonadotropin (HCG) day, and B-ultrasound findings, such as a gestational sac and endometrial thickness, will also be recorded (Table 2).

**Table 2 T2:** Baseline characteristics of the participants.

**General information**	**Age, race, body mass index, smoking, glucose**
Medical history	Primary infertility/secondary infertility; Infertility duration; Cause of infertility Male factors (oligospermia/asthenospermia/other male factors) Female factors (fallopian tube factor/polycystic ovary syndrome/endometriosis/other female factors) Unexplained infertility COH protocol Ultralong GnRH agonist; Short GnRH agonist; GnRH antagonist; Microsimulation cycle; Long GnRH agonist; Natural or other
Tuberculosis-related examination	Chest X-ray imaging Upper lung discrete linear or reticular fibrotic scars, sclerotic/calcified foci, and pleural thickening, with or without calcification of hilar/mediastinal lymph nodes. Erythrocyte sedimentation rate IGRA Salpingography Endometrial biopsy Laparoscopy, if available Hysteroscopy, if available
IGRA	IGRA positive or negative
Serum markers of ovarian function	Baseline hormone (Day 2–4 of menstruation) follicle-stimulating hormone (FSH), luteinizing hormone (LH), estradiol (E2), prolactin, testosterone (T), androstenedione (A), anti-Müllerian hormone (AMH), antral follicle count; Hormone levels (FSH, LH, E2, and P) on menstrual Day 2 of COH
Data of IVF-ET	No. of total sinus follicles No. of retrieved oocytes No. of good-quality embryos Endometrial thickness Endometrial pattern (A/B/C) No. of embryos transferred

*AMH, anti-Müllerian hormone; COH, controlled ovarian hyperstimulation; E2, estradiol; FSH, follicle-stimulating hormone; IGRA: interferon-gamma release assay; GnRH: gonadotropin-releasing hormone; LH, luteinizing hormone; No., number; P, progesterone; HCG, human chorionic gonadotropin*.

#### Follow-Up Plan

IVF-ET patients will be followed in early pregnancy ( ≤ 12 weeks), middle pregnancy (13–27 weeks), late pregnancy (≥28 weeks), and at 3 months after delivery. All pregnant women will be followed to fill out the case report form (CRF), and pregnancy outcomes will be assessed by telephone interviews (Figure 2).

**Figure 2 F2:**

Follow-up of the pregnancy outcomes and time of assessment.

##### CRF Information

Whether there are symptoms, such as fever, cough, night sweat, or blood in sputum during the pregnancy;

Whether blood routine test, chest X-ray examination, lung computed tomography examination, and sputum test have been performed and the results;

Whether the patient has been diagnosed with active TB;

Whether the TB has been diagnosed by clinical diagnosis, microbiology, or both;

Whether the pregnancy outcome is live birth, premature birth, abortion, or stillbirth; and

What are the birth weight and health statuses of the newborn?

#### LTBI Screening

LTBI testing will be conducted for the participants with untreated PTB using IGRA. The QFT assay (Qiagen, Hilden, Germany) will be performed according to the manufacturer's instructions. Individuals will be categorized into two groups based on the IGRA results: (1) Group 1: those with negative IGRA results and (2) Group 2: those with positive IGRA results. A special team will be assigned to perform follow-up on the pregnancy outcomes.

#### Interpretation of CXR

Prior PTB is defined as the presence of radiologic evidence suggestive of old/inactive PTB (11–13, 21, 22), including upper lung discrete linear or reticular fibrotic scars, sclerotic/calcified foci, and pleural thickening. This is an analysis of chest imaging findings, and a distinct history of TB is not necessary for the determination. Patients with other granulomatous diseases or tumors will be excluded. A chest radiologist and a respiratory clinician will confirm all CXR results.

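### Prior pulmonary TB is defined by chest X-ray signs alone, so the TB origin of the IGRA-negative comparator is uncertain and the live-birth contrast may not isolate LTBI

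*Protocol article*

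**What the plan says.** Under Interpretation of CXR: "Prior PTB is defined as the presence of radiologic evidence suggestive of old/inactive PTB". The signs listed are "upper lung discrete linear or reticular fibrotic scars, sclerotic/calcified foci, and pleural thickening", and the section adds: "This is an analysis of chest imaging findings, and a distinct history of TB is not necessary for the determination". It gives two safeguards: "Patients with other granulomatous diseases or tumors will be excluded" and "A chest radiologist and a respiratory clinician will confirm all CXR results".

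Under Study Design, the question treats every participant as having had PTB: "We will investigate whether LTBI (positive IGRA) in patients with untreated prior PTB affects the pregnancy outcomes".

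Table 2 lists chest imaging among the baseline data, including whether nodal calcification is present ("with or without calcification of hilar/mediastinal lymph nodes"). The adjustment set under Sample Size Calculations is age, BMI, infertility causes, COH protocol, endometrial thickness and number of good-quality embryos. It contains no CXR feature.

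The Introduction reports that "the IGRA positivity rate was 75.5% in infertile women with untreated PTB on CXR" (unpublished data), against 13-20% in a study from rural China. It also reports lower clinical pregnancy and live birth rates in untreated prior PTB than in women without PTB, but gives no rates. Strengths and Limitations claims stronger evidence for causality and names only the single centre as a limitation.

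**The concern.** The question requires both IGRA groups to have had PTB and to differ in LTBI. The eligibility rule establishes only that the film suggests old PTB. An IGRA-positive woman has a second, independent sign of TB infection; an IGRA-negative woman has none. About a quarter of the cohort is expected to be IGRA-negative, and the article does not say whether these women had TB and now test negative or never had TB.

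Any errors in the CXR classification would therefore not divide evenly between the groups. The retrospective study described in the Introduction found lower live birth with CXR-defined PTB than without it. Never-TB women in the comparator could therefore raise its live birth rate and make IGRA positivity look harmful even if LTBI had no effect. The Discussion makes later studies of anti-TB therapy depend on this result, so the attribution matters.

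**Working it through.** **The plan's own figure.** 19 variables × 10 = 190 live births; 190 / (0.30 × 0.53) = 1,195, which the article rounds to 1,200. This point does not affect that figure.

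**Inputs from the article.** N = 1,200; cohort IGRA positivity q = 0.755; background positivity b = 0.13-0.20; transfer rate 0.53; live birth rate 0.30.

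**Assumed, not in the article.** The share f of enrolled women whose lesion is not from TB; that these women have background positivity b; and the live-birth difference d between never-TB and true prior-PTB women.

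**Group sizes.** IGRA-positive 1,200 × 0.755 = 906; IGRA-negative 294. With transfer: 636 × 0.755 = 480 and 156.

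**Where never-TB women would fall.** A fraction 1 − b = 80-87% of them would be IGRA-negative. Their share is f(1 − b)/0.245 of the IGRA-negative group and f·b/0.755 of the IGRA-positive group. With no LTBI effect, the apparent IGRA difference is d times the gap between these two shares. The last column is the IGRA positivity in true prior PTB that each f implies, (0.755 − f·b)/(1 − f).

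| f (assumed) | share of IGRA-negative | share of IGRA-positive | apparent difference | implied positivity in true prior PTB |
|---|---|---|---|---|
| 0% | 0% | 0% | 0 | 75.5% |
| 5% | 16-18% | about 1% | 0.15-0.17 d | 78-79% |
| 10% | 33-36% (96-104 of 294) | 2-3% | 0.30-0.34 d | 82% |
| 20% | 65-71% | 3-5% | 0.60-0.68 d | 89-91% |

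**The same check from the other side.** Fix the IGRA positivity in true prior PTB and solve for the never-TB share of the comparator. It is 0% at 75.5%, about 24% at 80%, 67-68% at 90% and 100% at 100%. With the review figure of 77.7% in place of 75.5%, positivity of 80-90% gives 13-63%.

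**Size on the outcome (illustration).** Take d = 5-10 percentage points as an assumption. At f = 10% the spurious difference is 0.30 × 5 = 1.5 to 0.34 × 10 = 3.4 points. With true-PTB positivity of 90% (f about 19-21%), live birth 30% in true prior PTB and 35-40% in never-TB women, it is 3.1-6.4 points (odds ratio 0.87-0.75). An unadjusted comparison of 480 with 156 transfers would then be significant with probability about 11-32%, although LTBI has no effect.

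**The case against.** A reader might infer that never-TB women do collect in the comparator, or that the listed signs are non-specific. The documents support neither. The article calls the signs suggestive of old PTB, begins the list with upper-lung lesions, excludes other granulomatous diseases and tumors, and has two specialists confirm each film. Positivity of 75.5% against 13-20% shows strong enrichment for TB infection. Neither f nor d is given, and the effect is nil if IGRA positivity in true prior PTB is itself 75.5%. All of this stands, and it is why the point is conditional. It still does not account for the IGRA-negative quarter, which is where any error would sit.

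Nor is the absence of a TB history a defect in itself. The target population is untreated, and the Study Design text excludes any previous TB diagnosis (Table 1 and Procedures exclude treated TB only; these need to be reconciled). Requiring a history would conflict with that wording and is not proposed here.

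If past TB lowers live birth only through LTBI, IGRA-negative women would have similar outcomes whether or not they had TB, and the bias would shrink. The planned contrast cannot show whether that is so.

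Finally, lesion coding and sensitivity analyses may stand in a full protocol or analysis plan that is not shown. The point therefore rests on what the article does state: the definition, the target question, the adjustment set and the causal claim.

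**Conclusion.** The concern holds in conditional form. The TB origin of the IGRA-negative women is uncertain. If some enrolled women never had TB, 80-87% of them would fall in the comparator, so the contrast may partly compare past TB with no TB. Given the live-birth result reported in the Introduction, the likely direction is towards apparent harm from LTBI.

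The size cannot be fixed from the documents. It runs from nil to large, with 33-36% of the comparator at an assumed 10% of the cohort as a middle case. This rests on never-TB women having background IGRA positivity and on past TB lowering live birth by some route other than current LTBI. It does not invalidate the study, but attributing a difference to LTBI goes beyond what the definition of prior PTB supports.

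**What to change.** 1. From the two specialists' existing readings, code lesion type before the IGRA result is known. Keep upper-lung fibrotic scars separate from isolated calcified foci and from isolated pleural thickening, so that the restricted set does not retain the lesions whose origin is less certain. The described sequence already places CXR before IGRA, so this mainly means recording it.
2. Prespecify two sensitivity analyses of IGRA and live birth: one restricted to the most TB-typical lesions, and one adding lesion type to the model.
3. Report the primary result as an association with IGRA status among women with CXR findings suggestive of prior PTB. Do not attribute it to LTBI unless the restricted analysis agrees.
4. List the uncertain TB origin of the IGRA-negative group as a limitation.

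**Cost.** One coding field and two analyses; no new reader or procedure. The restricted analysis has wider intervals, and agreement there supports LTBI without proving it. The expected 1,200 × 0.53 × 0.30 = 190.8 live births give about 9.5 per variable with one added term (190.8/20) and about 9.1 with two (190.8/21), against the stated 10. Restoring 10 with one added term would need 200/0.159, about 1,258 women. Lesion adjustment is therefore better kept as a sensitivity analysis, leaving the primary model and sample size unchanged.

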#### IVF-ET Protocols

All the eligible participants will undergo a standardized COH protocol, oocyte retrieval, fertilization, and embryo transfer, as described previously (13, 23). COH will be followed by a planned transfer of one to two embryos (24). All embryos will be transferred on the third or fifth day after oocyte retrieval. The luteal-phase support with vaginal progesterone will be used from the day of ET until 10 weeks after conception. Clinical pregnancy is determined when an embryo sac is detected *via* ultrasonography at 30 days after ET.

